### Study visits

The Study Structure Overview is shown in Figure 1. Full screening may take 2 to 5 weeks after phone screening. Enrollment takes place at the completion of Screening. Safety information and measures will be collected up to 1 month after the participant's last therapy session during the Follow-Up Period. We will recruit actively up to enrollment of 12 participants. The Preparatory Period begins at enrollment and can be as short as 2 weeks. If the participant uses psychotropic medication, the preparation period can be up to 8 weeks to ensure adequate tapering until discontinuation plus one week of stabilization without medication.

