**Methods:**

A total of 12 participants [>18 years] with DSM-5 diagnosis of MDD will receive a flexible dose of MDMA in a therapeutic setting on two dosing days over a 4 week period preceded by three preparatory sessions. Each MDMA dosing session will be followed by three integration sessions. The primary outcome is change in MDD symptom severity, as measured by the mean change in MADRS scores from Baseline to 8 weeks after the second MDMA session. The secondary outcome is change in functional impairment, as evaluated by the mean change in Sheehan Disability Scale scores from Baseline to 8 weeks after the second MDMA session. Safety measures include vital signs, the incidence of Adverse Events and suicidality as measured by the Colombia-Suicide Severity Rating Scale.

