## Methods and analysis

### Design

This single-site, open-label study investigates the proof of principle and safety of MDMA-AT in 12 participants diagnosed with MDD and provides an initial assessment of potential treatment effectiveness.

A study protocol of MDMA-AT for PTSD (35), from which the study team has experience as a study site, informed the development of the present study protocol. In the treatment period, MDMA is given on two dosing days ~1 month apart. A supplemental half-dose of MDMA will be provided to extend the effects unless tolerability issues. A total of nine 90-min non-drug preparatory and integrative psychotherapy sessions will precede and follow the MDMA dosing sessions. Dosing sessions are followed by an overnight stay.

As in (35), for each participant, the study will consist of:

° Screening period: phone screen, informed consent, eligibility assessment, and enrollment of eligible participants.° Preparatory period with enrollment confirmation: medication tapering, preparatory sessions and baseline assessments.° Treatment period: two monthly dosing sessions and associated integrative sessions over ~8 weeks. The aims of the integration sessions are to continue the exploration of emotions and memories and to apply any new insights and experiences into daily life.° Follow-up period and study termination: 4 weeks with no study visits, followed by outcome measures and study termination visit.

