**Inclusion criteria [informed by (35)]**
• At Screening, meet DSM-5 criteria for current MDD with a symptom duration of more than 12 weeks and less than 2 years • At Baseline, have at least moderate MDD per MADRS and symptoms in the last month constituting a MADRS Total Severity Score of 20 or greater • ≧18 years of age • Sufficient competency in the Norwegian language • Capacity to provide consent • Agreement to provide a support person who is willing and able to be reached by the investigators in the event of a participant becoming suicidal or unreachable • Agreement to follow specific lifestyle modifications **Exclusion criteria**

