
As this is a feasibility study, we are interested in obtaining a preliminary impression of how MDD patients can be recruited to an MDMA-AT study, and to what extent the patient remains in the study as a proxy for the acceptability of the treatment. We will report the number of potential participants that were phone screened, as well as the number of participants that were considered as screen failures (not eligible after signed informed consent form and therefore not enrolled in the study), pre-dosing early terminations (initially enrolled, but deemed ineligible before the first MDMA session), post-dosing early terminations (Participants who choose to stop treatment, but who attend study visits and participate in outcome assessments), dropout (Participants who withdraw their consent and do not want to contribute to further study visits or measurements), and lost to follow-up (Participants who do not show up for study visits and who are unable to be contacted by the site staff).

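### The plan uses 12 both for participants treated with MDMA and for the cap on enrolment, but enrolment precedes several checks, so 12 dosed is not assured

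*Protocol article*

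**What the plan says.** The number 12 appears in two roles in the protocol article.

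- **Treated.** Abstract, Methods: "A total of 12 participants [>18 years] with DSM-5 diagnosis of MDD will receive a flexible dose of MDMA in a therapeutic setting". The Design section uses it the same way: the study "investigates the proof of principle and safety of MDMA-AT in 12 participants diagnosed with MDD".
- **Enrolled.** Study visits: "We will recruit actively up to enrollment of 12 participants".

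Study visits also fixes when enrolment happens: "Enrollment takes place at the completion of Screening". The sentence straight after the cap adds: "The Preparatory Period begins at enrollment and can be as short as 2 weeks". Table 2 agrees. It shows enrolment at Visit 0, medication taper at Visits 0 to 2, the Baseline MADRS at Visit 3, confirmation of enrolment at Visit 4 and the first dosing session at Visit 5.

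One inclusion criterion in Table 1 is tied to the later time point: "At Baseline, have at least moderate MDD per MADRS", with a score of 20 or more. Under Recruitment and participant population, the article lists among the counts to be reported "pre-dosing early terminations (initially enrolled, but deemed ineligible before the first MDMA session".

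**The concern.** A size stated as participants treated and a rule that stops at participants enrolled agree only if nobody is lost in between. Here the gap is not a formality. It contains a medication taper for those who need one, a severity criterion that is formally applied only after enrolment, and repeated eligibility checks. The plan itself expects that some enrolled people may not reach a dose, because it defines a category for them.

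Two things are at stake. First, a reader of the abstract expects 12 treated patients, and the recruitment rule does not secure that. Second, the article treats staying in the study as a proxy for acceptability, and a retention figure depends on whether its base is 12 enrolled, 12 confirmed or 12 dosed. With a base of 12, each person is 1/12, or about 8%.

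**Working it through.** **1. Can the figure of 12 be reproduced?** No. The article gives no power, precision, standard deviation or dropout input. It says that the design follows an earlier open-label trial with 12 participants. The check is therefore of the count, not of a sample-size formula.

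**2. Order of events (Table 2, Table 1, Study visits).**

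| Step | Visit | Relative to the cap |
|---|---|---|
| Enrolment, recruitment cap of 12 | V0 | the cap |
| Medication taper, if needed | V0 to V2 | at or after |
| Eligibility re-assessed | V1, V2, V4 | after |
| Baseline MADRS, criterion of 20 or more | V3 | after |
| Repeat drug and pregnancy screens, confirmation | V4 | after |
| First MDMA session | V5 | after |

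The whole preparatory period can last up to 8 weeks for users of psychotropic medication according to Study visits, and 2 to 11 weeks according to Table 2.

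**3. Chance of a shortfall.** The article gives no pre-dosing loss rate, so p is an assumption. With 12 enrolled at V0, independent losses with probability p each, and no replacement:

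- P(fewer than 12 dosed) = 1 − (1 − p)^12
- Expected number dosed = 12(1 − p)

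| Assumed p | P(fewer than 12 dosed) | Expected dosed |
|---|---|---|
| 1% | 11% | 11.9 |
| 2% | 22% | 11.8 |
| 5% | 1 − 0.540 = 46% | 11.4 |
| 10% | 1 − 0.282 = 72% | 10.8 |
| 20% | 1 − 0.069 = 93% | 9.6 |
| 30% | 99% | 8.4 |

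The chance passes one half at p = 1 − 0.5^(1/12) = 5.6%.

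**4. Effect on precision.** For the mean MADRS change, the half-width of a 95% confidence interval in units of the SD of the change is t(0.975, n − 1)/√n:

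- n = 12: 0.635
- n = 11: 0.672, a ratio of 0.672/0.635 = 1.06
- n = 10: 0.715, a ratio of 0.715/0.635 = 1.13
- n = 9: 0.769, a ratio of 0.769/0.635 = 1.21

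This assumes that the SD does not change and that n is the number of participants contributing a change score. The article does not state which participants those are.

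**5. Size of the remedy.** If recruitment continued until 12 were dosed, the average number enrolled would be 12/(1 − p): 12.6, 13.3 and 15.0 at p = 5%, 10% and 20%. That is roughly one to three extra people.

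**The case against.** **Enrolment may mean confirmed enrolment.** Table 2 marks enrolment at V0 and again, as confirmed, at V4, and the article calls people lost before dosing initially enrolled. The 12 could then be the confirmed number. This cannot be ruled out, but the sentences around the cap define enrolment as the end of screening and the start of the preparatory period. The ambiguity is itself a reason to say which is meant.

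**Replacement may be covered elsewhere.** This is a condensed article, and a replacement rule may stand in the full protocol. Its absence here is not the fault. The fault is that two statements that are present do not agree.

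**Some hurdles may be cleared before enrolment.** Recruitment and participant population speaks of at least moderate depression at enrolment and of taper being requested during screening. If so, later losses would be fewer. This stands as a reason not to assume a high loss rate. It also conflicts with Table 1 and Table 2 on timing, so it adds to what must be reconciled.

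**The effect is small.** There is no power target to miss, the article disclaims definitive conclusions on effectiveness, and it will report pre-dosing terminations separately, so the dosed number will be visible. All of this stands, and it limits the weight of the point.

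**Stronger readings to avoid.** A reader might infer that fewer than 12 will probably be dosed. That needs a loss above about 5.6% per person and no replacement, and the article documents neither. A reader might also infer that fewer than 12 will be analysed, or that efficacy and safety will be based on dosed participants only. No analysis set is stated, and Table 2 collects adverse events from V0, so neither can be claimed. Nor are the 8 and 11 weeks the length of the taper: they describe the whole preparatory period.

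**Conclusion.** The point holds in a limited form. By the article's own definitions, the recruitment rule stops at 12 people enrolled at V0, while the abstract and the Design section speak of 12 treated. The plan foresees losses between the two, so 12 dosed is not assured.

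How likely a shortfall is depends on a rate that the article does not give: 46%, 72% or 93% at assumed independent losses of 5%, 10% or 20% without replacement, but only 11% at a loss of 1%. The cost in precision is modest, about 13% in interval width if 10 rather than 12 contribute. No conclusion of a pilot of this kind turns on that. The correction is worth making because the stated size and the base for retention should be unambiguous.

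**What to change.** Choose one of two wordings.

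1. **Keep the cap and restate the size.** Say that 12 participants will be enrolled at V0 and that the number receiving MDMA may be lower. Do not insert an expected number dosed, because no loss rate supports one.
2. **Keep 12 as the treated number and move the count.** Count the 12 at confirmed enrolment (V4), continue recruitment to replace those lost before the first dose, and report these losses separately, as the article already plans. Table 2 repeats the drug and pregnancy screens at V5, so make clear that a loss between V4 and the first dose is also replaced.

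In either case, reconcile the abstract, Design, Recruitment and participant population, Table 1 and Study visits on what 12 counts, and on whether severity and taper are dealt with before or after enrolment. The investigators must settle which timing applies.

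The first option costs one changed sentence. The second may mean screening a few more people.

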**Figure 1 F1:**
[figure not shown]
Study structure overview.

The preparatory period ends at enrollment confirmation and thus the start of the treatment period. The treatment period lasts approximately 8 weeks and includes two dosing sessions 3-5 weeks apart and three non-drug integrative sessions after each of the two. After the final Integrative Session 2.3 (Visit 12), participants will enter the follow-up period with no study visits for ~4weeks, followed by the Primary Outcome MADRS T2 (Visit 13). The study procedures are presented in Table 2.

**Table 2 T2:** Time and events – study procedures [informed by (35)].

**Time and events – study procedures**	**Screening period (2 to 6 weeks)**			**Preparatory period w/enrollment confirmation** **(2 to 11 weeks)**			
	**Screening**		**Enrollment**	**Preparatory**		**Baseline MADRS T1**	**Baseline & enrollment confirmation**
**Visit**	**Phone screening**	**Screening**	**V0**	**V1**	**V2**	**V3**	**V4**
**Visit description**	**Phone calls**	**In-person visits & labs**	**Enrollment**	**Prep 1**	**Prep 2**	**MADRS T1 assessment at site**	**Prep 3 & enrollment confirmation**
Initial phone screen	✓						
Informed consent	Send Copy	✓					
Follow-up phone screen	✓						
Assess eligibility	✓	✓	✓	✓	✓		✓
Medical/psychiatric history	✓^A^	✓		✓	✓		✓
Past/current medication & adherence	✓	✓		✓	✓		✓
Weight, resting vitals		✓					
Physical exam		✓					
ECG & rhythm strip^H^		✓					
Clinical lab tests		✓					
Drug screen		✓					✓
Pregnancy screen		✓					✓
Enter participant in eCRF		✓					
Record				✓	✓	✓	✓
Medication taper			✓	✓	✓		
Study enrollment			✓				✓ Confirmed
All AEs^B^			✓	✓	✓		✓
90-min preparatory session				✓	✓		✓
Phone call follow-up^C^					✓		
**Time and events – study procedures (continued)**	**Treatment period** ~**8 weeks (**+**/-3 weeks)**								**Follow-up period & study termination (**~**4 weeks)** **13 weeks (**+**/-3 weeks) post baseline**	
	**Treatment 1**				**Treatment 2**				**Outcome**	**Study Termination**
**Visit**	**V5**	**V6**	**V7**	**V8**	**V9**	**V10**	**V11**	**V12**	**V13**	**V14**
**Visit description**	**Exp. 1**	**Int 1.1**	**Int. 1.2**	**Int 1.3**	**Exp. 2**	**Int. 2.1**	**Int 2.2**	**Int 2.3**	**MADRS T2 assessment at site**	**Study termination**
Past/current medication and adherence	✓	✓	✓	✓	✓	✓	✓	✓		✓
Drug screen	✓				✓					
Pregnancy screen	✓				✓					
Record	✓	✓	✓	✓	✓	✓	✓	✓	✓	
All AEs^D^	✓	✓	✓	✓	✓	✓	✓	✓		✓
Administer IP	✓				✓					
8-hour Exp. Session	✓				✓					
BP, Pulse, Temperature^E^	✓				✓					✓^F^
Overnight Stay	✓				✓					
90-min Integrative Session		✓	✓	✓		✓	✓	✓		
Phone Call Follow-up^G^		✓				✓				
Weight										✓

^A^At Screening, collect data on previous hospitalizations, healthcare utilization and economic productivity. Request participants to obtain medical/psychiatric records to bring to the in-person screening.

^B^All Adverse Events (AEs) includes collecting Serious Adverse Events, AEs of Special Interest, AEs of Psychiatric Status, AEs requiring medical advice or attention, AEs that indicate withdrawal of a participant, and all other AEs.

^C^If needed, call participant to confirm medication tapering and stabilization is complete prior to Visit 3.

^D^All Adverse Events (AEs) includes collecting Serious Adverse Events, AEs of Special Interest, AEs of Psychiatric Status, AEs requiring medical advice or attention, AEs that indicate withdrawal of a participant, and all other AEs.

^E^During Dosing Sessions, vitals are measured before Investigational Product administration, immediately before the supplemental dose is administered (or would be, if supplemental dose not given), and approximately 8 h after initial dose, and as needed.

^F^At Study Termination, only blood pressure needs to be measured.

^G^4 days of phone call follow-up: Day 2 and 7 after the Dosing Session, with two additional calls in between.

^H^We do not repeat the ECGT during the MDMA dosing sessions, since we will avoid possible interference with the therapy facilitated by MDMA.

### MDMA-assisted therapy

Overall, the goal of the therapy is to reduce MDD symptoms and improve the function of the participant. The study therapists have been trained in an MDMA-assisted therapy training program in a previous clinical trial.

During the preparatory period, the therapists begin establishing an effective therapeutic alliance, addressing any questions or concerns the participant may have, as well as familiarizing them with the therapeutic approach.

MDMA-AT is largely inner-directive, i.e., allows each participant's experience to unfold spontaneously without providing a specific direction or advice about the content of the experience. Important elements are creating a setting of safety and support, empathic listening, inviting the participant to explore emerging material and make suggestions instead of having a set agenda (48). In addition, support for surfacing challenging material is provided in a way that does not get in the way of the participant's emerging experience. The MDMA sessions will take place in a private, aesthetically pleasing and quiet room with flexible ambient temperature. The participant can either lie down on the bed or sit up with support from pillows and alternate between introspection and interaction with the therapists. The use of eyeshades and headphones is suggested while the participant “goes inside.”

The goals of the integrative sessions are to help the participant continue to process emerging material and provide support if any challenges arise during this process, and invite the participant to apply any new insights, perspective and attitudes to daily life.

### Outcome measures

#### Primary outcome measure

The primary outcome measure will capture the change in MDD symptom severity, as measured by the mean change in MADRS scores from Visit 3 (Baseline) to Visit 13 (approximately 12 weeks post Baseline) (49).

#### Secondary outcome measure

The secondary outcome measure will capture the change in functional impairment, as measured by the mean change in the clinician-rated Sheehan Disability Scale (SDS) scores from Visit 3 (Baseline) to Visit 13 (< 12 weeks post Baseline) (50).

#### Safety outcome measures

The C-SSRS is a clinician-administered measure of suicidal behavior designed to detect any suicidal thoughts or behaviors during a clinical trial (51). It consists of a Baseline/Screening version and a Since Last Visit version. The Baseline/Screening version will be administered during screening, and the Since Last Visit version will be used at all subsequent visits. The C-SSRS assesses suicidal ideation, ideation intensity, and behavior.

Safety outcome measures that will evaluate the safety of MDMA-AT in a clinical practice setting are shown in Table 3 [informed by (35)].

**Table 3 T3:** Safety outcome measures.

1. Assess incidence of AEs during Dosing Sessions that may be indicative of a medical complication of the Investigational Product (IP), such as clinical signs and symptoms of chest pain, shortness of breath, or neurological symptoms or any other signs or symptoms that prompt additional vital sign measurements
2. Assess incidence of AEs by severity
3. Assess incidence of Treatment Emergent AEs (TEAEs) by severity
4. Assess incidence of TEAEs by severity taken during a Dosing Session and 2 days after IP administration
5. Assess incidence of AESIs, defined as AEs specified in the protocol related to cardiac function, suicide risk, and abuse liability
6. Assess incidence of AEs by severity categorized as leading to discontinuation of IP, resulting in death or hospitalization, and continuing at Study Termination
7. Assess incidence of SAEs
8. Assess incidence of psychiatric concomitant medications taken during a Dosing Session and 2 days after IP administration
9. Assess incidence of any psychiatric concomitant medications taken during the Treatment Period
10. Assess incidence of serious suicidal ideation and positive suicidal behavior assessed with the Columbia Suicide Severity Rating Scale (C-SSRS)
11. Assess mean changes in blood pressure, heart rate, and body temperature from pre-IP administration to the end of each Dosing Session

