• Electroconvulsive Therapy (ECT) or ketamine within 12 weeks of enrollment • Current or previously diagnosed psychotic disorder, significant history of mania, or evidence of a personality disorder • Current eating disorder with active purging • Current moderate or severe alcohol or cannabis use disorder within the 12 months prior to enrollment • Active illicit (other than cannabis) or prescription drug substance use disorder at any severity within 12 months prior to enrollment • Current serious suicide risk, as determined through psychiatric interview, responses to C-SSRS, and clinical judgment of the investigator will be excluded; however, history of suicide attempts is not an exclusion • The use of any psychoactive medication not approved by the research team from Baseline through Study Termination (with the exception of gabapentin or certain opiates for pain control) • Positive pregnancy test or breastfeeding. Unable to agree to the use of highly effective contraception methods • History of any medical condition that could make receiving a sympathomimetic drug harmful because of increases in blood pressure and heart rate. This includes, but is not limited to, a history of myocardial infarction, cerebrovascular accident, or aneurysm. Mild, stable chronic medical problems (diabetes mellitus type 2, for example) are allowed in the study if the symptoms from that disease are not being confused with side effects from MDMA or interfering with study participation • Uncontrolled hypertension. Participants with well-controlled hypertension might be enrolled if acceptable cardiovascular risk (family history, smoking, lipid levels, body weight, level of physical activity) and no signs of ongoing cardiovascular or cerebrovascular disease from history, physical exam or ECG supplemented by echocardiography or nuclear imaging, and carotid ultrasound • History of ventricular arrhythmia at any time, other than occasional premature ventricular contractions (PVCs) in the absence of ischemic heart disease • Have a marked Baseline prolongation of QT/QTc interval e.g., repeated demonstration of a QTc interval >450 milliseconds [ms] in males and >460 ms in females (corrected by Fridericia's formula) • Have a history of additional risk factors for Torsade de pointes (e.g., heart failure, hypokalemia, family history of Long QT Syndrome) • Symptomatic liver disease or significant liver enzyme elevation • History of clinically significant hyponatremia or hyperthermia • Weight < 48 kilograms (kg)

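### The psychiatric-medication outcome (Table 3, item 9) stops at Visit 12, about four weeks before the primary MADRS at Visit 13, although medication is recorded at Visit 14

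*Protocol article*

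**What the plan says.** **The medication outcome.** Safety outcome measures, Table 3, item 9: "Assess incidence of any psychiatric concomitant medications taken during the Treatment Period". Item 8 is narrower still and covers only a dosing session and the two days after it. No other item in Table 3 counts psychiatric medication.

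**The timing.** Study visits: "The treatment period lasts approximately 8 weeks and includes two dosing sessions 3-5 weeks apart". Table 2 places Visits 5 to 12 in that period and Visits 13 and 14 in a separate follow-up period. After Visit 12, "participants will enter the follow-up period with no study visits for ~4weeks, followed by the Primary Outcome MADRS T2 (Visit 13"). The primary outcome is the "mean change in MADRS scores from Visit 3 (Baseline) to Visit 13 (approximately 12 weeks post Baseline").

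**What is collected.** The Table 2 row "Past/current medication and adherence" is ticked at Visits 5 to 12 and at Visit 14, and is blank at Visit 13. Study visits adds: "Safety information and measures will be collected up to 1 month after" the last therapy session.

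**The exclusion criterion.** Table 1 lists among its exclusions "The use of any psychoactive medication not approved by the research team from Baseline through Study Termination", with an exception for gabapentin and certain opiates used for pain. The article does not say what follows if the condition is broken after dosing.

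**The concern.** The trial has no control arm, and Visit 13 is the only MADRS after baseline until the long-term follow-up. Reading the change in that score requires knowing what else participants were taking when it was measured. The gap between Visits 12 and 13 is a long stretch without visits, and it falls in a sample in which some will have stopped psychotropic medication in order to take part. Item 9 closes just before that gap opens. A report that follows Table 3 as written could show little or no psychiatric medication use while some participants were on a new or resumed drug at the primary assessment.

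The Table 1 wording raises a second, smaller question. Conduct after enrolment cannot be a condition of eligibility. If a dosed participant breaks that condition before Visit 13, the article does not make clear how the person is classified. In an unblinded study of 12, that should not be left to judgement after the event.

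The study is meant to inform fully powered trials, so a few such participants could affect the estimate carried forward.

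**Working it through.** There is no figure in the article to reproduce. The check sets the passages side by side and then illustrates the size.

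**1. Does item 9 reach the primary endpoint?** No.

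| Element | Covers |
|---|---|
| Item 9 | Treatment Period, Visits 5 to 12 |
| Item 8 | Dosing session plus 2 days |
| Gap without visits | Visit 12 to Visit 13, about 4 weeks |
| Primary MADRS | Visit 13 |
| Medication recorded | Visits 5 to 12 and Visit 14 |

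The reporting window ends about four weeks before the endpoint. The data continue to Visit 14, so what is missing is a stated summary.

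**2. Does a breach of the Table 1 condition fit a listed category?** Recruitment and participant population gives five:

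- Screen failures are not eligible before enrolment.
- Pre-dosing early terminations are found ineligible before the first MDMA session.
- Post-dosing early terminations choose to stop treatment but continue assessments.
- Dropouts withdraw consent.
- Those lost to follow-up cannot be reached.

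A dosed participant who starts unapproved medication and keeps attending fits none of them.

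**3. How large could the effect of unlisted medication be?** Inputs: N = 12 (from the article); k users = 1 to 3 (assumed); medication effect at Visit 13, m = 0 to 6 MADRS points (assumed). If the users stay in the analysis, the mean improvement rises by k × m / 12.

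| k | m = 0 | m = 2 | m = 4 | m = 6 |
|---|---|---|---|---|
| 1 | 0 | 0.17 | 0.33 | 0.50 |
| 2 | 0 | 0.33 | 0.67 | 1.00 |
| 3 | 0 | 0.50 | 1.00 | 1.50 |

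**4. Is at least one user likely?** The article gives no rate. With an assumed probability p per person, the chance of at least one among 12 is 1 − (1 − p)^12. This is 0.46 for p = 0.05, 0.72 for p = 0.10 and 0.93 for p = 0.20.

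**5. What if such users were taken out of the analysis?** No passage does this, so the figures show only why clarity matters. If k users improve d points less than the rest, removing them raises the mean improvement by k × d / 12. For k = 1 to 3 that is 0.42 to 1.25 points at d = 5 and 1.25 to 3.75 at d = 15. It is 0 at d = 0. It is −0.42 to −1.25 at d = −5, where the users do better than the rest.

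**The case against.** The strongest reply is that item 9 is a safety measure. It describes medication use in the active phase and makes no claim about the primary analysis. How participants who start medication are analysed, and any sensitivity analysis, may be set out in the full protocol or SAP, which are not shown. Medication is recorded at Visit 14, adverse events are collected there, and the BDI-II at Visit 12 and Study Termination brackets the gap. All of that stands, so the absence of an analysis rule is not part of this point. It does not answer the narrower one: the stated window of a listed outcome ends before the endpoint it helps to interpret, although the data exist.

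A reader might infer something stronger: that restarts before Visit 13 are either unreported or removed, and that both inflate the benefit. The article does not support this.

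- **Unreported** is too strong, because medication is recorded at Visit 14.
- **Removed** has no basis. No passage takes users out of the analysis. The categories tie ineligibility found after enrolment to the time before the first MDMA session. Medication that the team approves lies outside the Table 1 condition altogether.
- **Both inflate** is an inference. Removal inflates the mean only if users do worse than the rest. Retention does so only if the medication works in the time available. A participant who is doing poorly and stays in lowers the mean improvement.

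An overstatement of 1.3, 2.7 or 4.0 points can be calculated for one, two or three users (16 × k / 12). It assumes that the others improve by 16 points, that users do not change at all, and that users are removed. The article gives none of these.

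**Conclusion.** The point holds as a matter of reporting. Item 9 omits the roughly four weeks before the primary MADRS, and in a single-arm study of 12 any effect of medication begun then would be read as part of the MDMA-AT change. The article fixes neither direction nor size. The 0.17 to 1.5 points rest entirely on one to three users and a medication effect of 2 to 6 points, and the shift is 0 if the medication does nothing by Visit 13.

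The Table 1 wording is a separate inconsistency of form. A condition that runs to Study Termination is listed as an exclusion criterion, and a breach after dosing matches no participant category. This leaves an unclear status. It does not show that anyone would be dropped from the analysis.

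**What to change.** 1. Extend Table 3, item 9 to run from Baseline through Study Termination (Visit 14), and list the start date of each psychiatric medication relative to Visit 13.
2. Reconcile Table 1 with the participant categories in Recruitment and participant population, leaving the medication restriction itself as it is. State that a breach after dosing is a recorded protocol deviation, and that the participant is still assessed at Visit 13 and kept in the primary mean. If the full protocol or SAP already says so, a cross-reference is enough.

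The cost is one additional listing and a few lines of wording. No new data are needed, because Table 2 already collects medication at Visit 4, at Visits 5 to 12 and at Visit 14. The downside is that the result may look slightly less favourable once medication begun before Visit 13 is shown beside it.
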